## 11.3 Clinical site monitoring

External trial monitoring will be conducted by WRAIR. External monitoring will be performed at the study sites through regular monitoring visits as agreed with the Sponsor. The external study monitor will be responsible to ensure that the trial is conducted according to ICH GCP guidelines including monitoring vaccine data consistency, vaccine accountability, dispatch and arrival of immunological specimens. A monitoring plan will be established prior to study initiation.

WRAIR will produce a detailed Monitoring Plan. The trial site will be monitored to ensure:

- the completeness and accuracy of the data entered on the CRFs
- compliance with the protocol and principles of GCP
- proper maintenance of all trial documentation
- complete IMP accountability
- smooth day-to-day running of the trial

All documents generated by the trial site which form part of this trial, and the ensuing data, must be made directly available in order that the monitor can verify, using source documents, the data in the CRFs. This procedure is termed Source Document Verification (SDV).

The PI agrees to allow GCP audits of the trial site and all trial documentation by the Sponsor or its representatives.

### 11.3.1 Direct Access to Data

Participating investigators should agree to allow trial-related monitoring, including audits, ethics committee review and regulatory inspections by providing direct access to source data/documents as required. Participants' consent for this is obtained as part of the consent process.

### **11.3.2 Archiving and Data ownership**

Study related documents including clinical notes, completed CRFs and original laboratory results, hard copies and electronic copies will be kept in a secure location at MUHAS, MMRC and INS. The data generated in this study will be the property of the TaMoVac Investigators and will be held on their behalf by MUHAS, NIMR, MMRC and INS until completion of the study or until it is stopped. Thereafter the data will be passed over to MUHAS, NIMR, MMRC and INS for archival purposes according to accepted regulation for a minimum of 15 years. Data for e.g. continuous progress reporting or presentations during the internal TaMoVac investigator meetings will be available during the study. In general the use of study data for any purpose will need to be approved by the TaMoVac Steering Committee.

WRAIR will require access to all data in order to meet obligations with full reporting of data to the FDA regarding any use of the MVA product. KI/SMI will maintain data in accordance with US FDA guidelines until 2 years after licensure or retiring the IND.

### **11.4 Monitoring by the Trial Management Group**

The Trial Management Group (described in section 15.1) will monitor the following using a reporting template:

- Screening, enrolment and screen:enrolment ratio for each clinical centre
- Immunisations completed (first, second, third, fourth, fifth) and any missed or outside the window
- Adverse events of note
- Missed visits and loss to follow-up
- Logistical difficulties at the clinical centres
- Data management issues (timeliness of CRFs completeness)
- Immunology core lab issues (completeness of specimens, next batch transfer or analysis)
- GCP issues (minor or other breaches)

### **11.5 Confidentiality**

All personal details of the participants and the results of the trial will be kept strictly confidential. The Sponsor, as represented by [name], will not keep any material on file containing the volunteers' full names; this information will be kept by PIs in the clinical trial facilities in a secure location. The confidentiality of volunteers will be respected and maintained at all times.

Each participant's physician will be informed of the nature and timing of the trial and asked to complete a brief questionnaire.

### **11.6 Quality Assurance and Quality Control of Data**

Sites must not screen any volunteers until all approvals appropriate to the site are in place, and the sponsor or representative has conducted a site initiation visit. The Sponsor approval is dependent on receipt of an approval from the Tanzanian FDA, the Mozambican Regulatory Authority (Pharmaceutical Department) and approval from the Research Ethics Committee (REC) in MUHAS, MMRC, NIMR and INS.

It will be the responsibility of the PIs to ensure the accuracy of all data entered in the CRFs at their respective sites. They must conduct the trial personally, or delegate to members of

their research team specific tasks using a delegation log. They must ensure that each member of their research team is suitably qualified to perform delegated tasks by education, training and experience, and must ensure that written procedures are followed to enable collection high quality data.

## 12 ETHICAL CONSIDERATIONS AND APPROVAL

### 12.1 Ethical issues

There are two aspects of this trial that raise ethical issues

Firstly, because the product under investigation is a **candidate HIV vaccine**, and HIV is transmitted sexually, it is necessary to collect sensitive personal information and the volunteers might need to undergo a genital examination. The nature of the product may lead volunteers to erroneously conclude they are protected against HIV and to engage in riskier behaviour as a consequence. It is possible that following immunisations, participants may have equivocal results in the standard laboratory tests for HIV. However, it will be possible for any accredited laboratory to distinguish between a post-vaccination response and natural infection using routine assays.

Secondly **the reimbursement** to compensate for the intense follow-up schedule, which is a feature of healthy volunteer trials, could be sufficient incentive for individuals to take part against their better judgement.

### 12.2 Ethical Considerations

This study will be conducted according to ICH GCP guidelines and the Declaration of Helsinki (Version 2008), and it is the responsibility of the Clinical Investigators to ensure adherence. Before the study starts all personnel involved in the clinical and laboratory trial units will be trained for Good Clinical Practice (GCP) and/or Good Laboratory Practice (GLP) respectively. Study personnel will also be trained on standard operating procedures (SOPs) that are related to the protocol and will follow the GCP and GLP guidelines.

This protocol has been submitted to the National Ethics Committee at the Tanzanian National Institute of Medical Research (NIMR) for ethical approval. NIMR is registered with the Office for Human Research Protections (OHRP), US (FWA00002632). In parallel the proposals will be submitted to the institutional ethical committees. These are the Research and Publications Committee at the Muhimbili University of Health and Allied Sciences (MUHAS) having the FWA 00004301, and the Mbeya Municipal Medical Authorities in Mbeya (FWA00002469), and subsequently to the appropriate ethics committee in Sweden and Germany. In Mozambique the protocol has been submitted to the National Health Bioethics Committee (FWA00003139). The DNA and MVA vaccines, which will be donated by the KI/SMI in Sweden, have been approved by the Swedish Medical Products Agency and are currently used in the ongoing clinical trials in Sweden. The US Food and Drug Authority has previously approved the MVA which is in ongoing clinical trials in the USA. Approval of these immunogens will also be undertaken independently by the Tanzania Food and Drug Authority (TFDA) and the Mozambican Regulatory Authority (Pharmaceutical Department). The KI/SMI in Sweden will be responsible for providing the Investigator's Brochure (IB) for DNA as well as the Investigator's brochure for MVA as well as generating the randomization list.

Any changes or amendments in the protocol will be reported and approved as Memo to the IRBs or re-submission to the ethical and regulatory authorities. Safety assessment, monitoring and reporting will be assured as lined out in this protocol and responsibilities are defined. Continuous progress reporting will be provided as requested.

No study materials or data will be obtained from study volunteers before approval from the relevant bodies. Volunteer/participant information and data will be protected and coded and

only de-identified data will be provided for data entry. Access to volunteer/participant information for study schedule administration and tracing will be restricted to selected individuals only at the study sites. Access to study binders will be restricted to the clinical study site members and the internal and external monitors during monitoring visits. Representatives from the sponsor or ethical and regulatory authorities will be allowed to access study binders during inspections or audits and will be bound to confidentiality rules. Access to de-identified volunteer/participant data from the database outside the study sites will be restricted to identified study monitors and members of the Data Management Centres.

## **13 INDEMNITY**

### **13.1 Insurance for investigators**

The Principal Investigators will ensure that relevant clinical and laboratory staff engaged in the study are covered for possible legal action against the investigators for harm through indemnity insurance schemes, which will be paid for by the project during the study period.

### **13.2 Health care Insurance for trial volunteers**

In Tanzania, all trial volunteers will receive health insurance provided by the National Insurance Corporation of Tanzania Limited which will cover for injury or death related to the trial through insurance schemes. These will be confined to the period of the study. For Mozambique, all events, whether immediate or late events (up to 2 years after the end of the study), which are proven to be associated to the study product, including death, will be covered by Trial Insurance.

Vecura Company in Sweden will have an insurance that covers any defect in the production of the DNA vaccine only.

SMI will in the role of sponsor assume the liability for the DNA vaccine and through separate collaborative agreements for the MVA-CMDR, the CN54rgp140 and GLA-AF.

## 14 FINANCE

### 14.1 Compensation for study participation

Regular compensations will be made to all volunteers/participants to cover their travel expenses as well as time and inconvenience compensation. For scheduled visits this will amount to 20,000 TShs (~ 12 USD) for Dar es Salaam and 15,000 TShs (~ 10 USD) for Mbeya where transport and living costs are lower compared to Dar es Salaam. In Maputo compensation for scheduled visits will be 400,00 Mts (~ 14 USD) . Unscheduled visits will be compensated with 10,000 TShs in Dar es Salaam and 8,000 TShs in Mbeya and 200,00 Mts in Mozambique. Compensation for unscheduled visits might be rejected in the case of assumed abuse of compensation, which will be up to the study team's decision. During the study volunteers/participants will receive hypoallergenic latex condoms free of charge. Treatment and care for minor diseases can be provided by the study provided free of charge and might include diagnostic procedures as well as medications such as painkillers, antipyretics, antibiotics or anti malaria treatment, iron substitution etc. In case of hospitalization or if further care will be required, these will be covered under the medical insurance provided by the National Insurance Corporation of Tanzania Limited. In Mozambique agreements with the HCM and the Polana Caniço Health Center will assure that the volunteers who need hospitalization and/or further medical requirements are assisted; these will be confined to the period of the study.

## 15 TRIAL COMMITTEES

### 15.1 Trial Management Team (TMT)

This group will oversee the day-to-day site procedures of the trial and the members will be primarily the clinical, laboratory, pharmacy and data management teams from each study site. Each TMT will be chaired by the site PI and/or his designee supported by the clinical coordinator, study secretary, community outreach officer, laboratory coordinator, study pharmacist, study nurses and data manager. Regular TMT meetings will be conducted. Notes will be taken and will form the basis of the progress report to the Trial Management Group. It will be the responsibility of the PI and/or his designee to assure on timely adverse events deviations or other unexpected events reporting, on the study progress as well as on regular continuous progress reporting to the ethical committees and regulatory authorities as requested also communicated to the TMG and TaMoVac Steering Committee. The TMT will assist and present during the Community Advisory Board (CAB) meetings.

### 15.2 Trial Management Group (TMG)

The supervision of the trial will be a responsibility of the Trial Management Group (TMG). The members will include the Chief Investigator, the Study Chairs, the site Principal Investigators, clinical coordinators, representative from WRAIR and IC, laboratory coordinators and data managers. The TMG will meet through research safety calls as indicated as well as during annual investigator meetings. The TMG will oversee and recommend on the study progress, clinical, data management, laboratory and pharmacy issues as well as study coordination procedures. This committee will be the central body to oversee adverse events and protocol deviations, to generate decisions about grade of adverse events and relationship to study vaccine as well as support for the TMT in case management. The TMG will also be the central body to collect and discuss progress reports on triggering adverse events providing information and recommendations to resume or terminate enrolment and vaccination after study pauses. Notes of TMG meetings will be kept and reported to the TaMoVac Steering Committee and Study Sponsor. Routine reports such as 6-monthly progress reports will be generated by the site PI's or his designee and sent to the the ethical committees and regulatory authorities in Tanzania and Mozambique including notification for the Study Sponsor and the TaMoVac Steering Committee. Expedited reports will be generated by the site PI or his designee and reviewed by the TMG before sending these to the Study Sponsor, TaMoVac Steering Committee, DSMB and to the ethical committees and regulatory authorities in Tanzania and Mozambique.

Members of the TMG are

| Name       | Position                              | Email                     |
|-------------------|----------------------------------------------|----------------------------------|
| [name]   | Chief Investiagtor, MUHAS                    | [contact]        |
| [name]    | Protocol co-Chairand SMI's Medical Expert,KI | [contact] |
| [name]  | MUHAS's Medical Expert                       | [contact]             |
| [name]       | Protocol co-Chair, LMU                       | [contact]                 |
| [name]  | Protocol co-Chair, MRC CTU                   | [contact]            |
| [name]   | Site PI, MUHAS                               | [contact]               |

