## 6.5 Dose modifications and discontinuation

There are no planned modifications to dose, other than discontinuation.

The schedule may be modified if a participant has symptoms or signs on the day of scheduled immunisation, and the investigator considers it best to defer the immunisation. The participant will be asked to return for review within the window period of the scheduled immunisations. Examples of the type of symptoms and signs are given in **Table 2** (section 7.5.5 of the protocol).

Any discontinuation and reason for early termination of the immunisation schedule will be discussed with the monitors and the TMG and should be reported to the Sponsor and DSMB within the next 2 working days. Trial participants who are discontinued from additional study injections will continue to be followed according to the schedule to further evaluate safety and monitor adverse events. They will also continue to be covered by the medical/trial insurance until the end of the study period. The frequency of laboratory investigations, e.g. for immunogenicity assessments may be reduced on consultation with the monitors and TMG.

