### **7.5.7 Serious adverse events**

A serious adverse event is defined in **section 8**.

All serious adverse events should be reviewed by the Principal Investigator for the clinical centre, and discussed at the next Trial Management Group call.

A serious adverse event might cause a PI to consider discontinuing dosing or withdrawing a participant from the trial.

For all serious adverse events, the investigator will complete a serious adverse event CRF and report it to Monitors, TMG, Sponsor and DSMB, within 24 hours of learning of the event as described in **section 8.2**, and on to the ethical committees and regulatory authorities in the timelines required by each authority.

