**Note:** Interventions or hospitalization for elective treatment, e.g. cosmetic surgery, tubal ligation or sterilization, hospitalization due to labour are not considered as adverse events unless complications related to the elective treatment occurs.

***Any HIV infection occurring throughout the study period will not be defined as a Serious Adverse Event but needs to be reported within 2 working days of awareness (see section 8.2)***

***Any Social Harm related to study participation or vaccination will be defined and graded as an Adverse Event (e.g. denial of health and life insurance, employment, immigration and marriage relationships).***

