## 8.2 Adverse events that require expedited reporting by the centres

Adverse and serious adverse events will be recorded on the Adverse Events case record form. Any severe clinical adverse event (grade 3 or 4), any serious adverse reaction or unexpected adverse reaction should be reported within 24 hours after site awareness to the Study Monitors, Sponsor, TMG, WRAIR and DSMB, and on to the Tanzanian and Mozambican ethics committees and regulatory authorities according to each authority's requirements. Any grade 3 or 4 fever must persist for 48 hours to meet the definition of severe fever..

Although post immunisation solicited local and systemic adverse events are documented separately from AEs, they are reported as above if they meet SAE or study pause rule definitions. Therefore the PI or designee must review both Vaccine/Reaction and Adverse Event CRFs to ensure prompt and complete identification of all the events described above that require expedited reporting.

**Expedited reporting** within 24 hours of the site awareness of the event is warranted for:

1. A clinical or social harm event resulting in a decision to discontinue the vaccination schedule
2. Administration of the incorrect vaccine or placebo
3. Any serious adverse events
4. Pregnancy
5. HIV infection

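### SAEs, pregnancy and HIV infection each carry two reporting limits (24 hours and 2 working days), and section 15.2 puts an untimed TMG review before expedited reports reach the DSMB and regulators

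*Protocol*

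**What the plan says.** **24-hour limits.** For an SAE, section 7.5.7 has the investigator "complete a serious adverse event CRF and report it to Monitors, TMG, Sponsor and DSMB, within 24 hours of learning of the event". Section 8.2 says that severe clinical events and serious or unexpected reactions "should be reported within 24 hours after site awareness to the Study Monitors, Sponsor, TMG, WRAIR and DSMB". It then gives a list for which expedited reporting "within 24 hours of the site awareness of the event is warranted for" five events: a harm-related discontinuation ("A clinical or social harm event resulting in a decision to discontinue the vaccination schedule"), a wrong product given, an SAE, a pregnancy and an HIV infection. Section 7.6 requires a fatal or immediately life-threatening SUSAR to reach the regulator within 24 hours.

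**2-working-day limits.** Section 8.1 says that an HIV infection is not classed as an SAE but "needs to be reported within 2 working days of awareness (see section 8.2"). Section 10.1 gives clinical-centre staff 2 working days to notify SAEs and 2 working days to notify pregnancies, and refers to section 8.2 both times. Section 6.5 says that any discontinuation of dosing "will be discussed with the monitors and the TMG and should be reported to the Sponsor and DSMB within the next 2 working days".

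**Order of reporting.** Section 15.2 says that the site PI or designee generates expedited reports, which are then "reviewed by the TMG before sending these to the Study Sponsor, TaMoVac Steering Committee, DSMB and to the ethical committees and regulatory authorities" in both countries. It states no time for that review. On the composition of the TMG it says: "The members will include the Chief Investigator, the Study Chairs, the site Principal Investigators", followed by others.

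**The concern.** A site needs one answer to two questions: how fast must this event be reported, and may the report leave before the TMG has looked at it? For three of the events that 8.2 treats as urgent, the protocol gives two answers to the first. A centre working from 8.1 or 10.1 could use the full 2 working days, believe it had complied, and be late under 8.2. On the second question, 7.5.7 and 8.2 name the TMG as one recipient among several, while 15.2 makes its review a step to complete before the DSMB, ethics committees and regulators are told.

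The trial runs at three centres in two countries, so different centres can follow different written rules, and the monitor has no single standard to check against. Section 7.6 says that MVA-CMDR and CN54rgp140/GLA-AF are given at the same timepoint here for the first time, so prompt independent oversight matters. No endpoint, sample size, power or alpha level is affected.

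**Working it through.** There is no plan figure to reproduce. The check matches each event on 8.2's list against every other deadline visible in the current text.

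| Event on 8.2's list | 8.2 | Other visible limit | Result |
|---|---|---|---|
| Discontinuation for clinical or social harm | 24 h | 6.5: 2 working days, for any discontinuation | Overlap of a general and a specific rule |
| Wrong vaccine or placebo given | 24 h | None found | No conflict |
| SAE | 24 h (7.5.7 agrees) | 10.1: 2 working days, citing 8.2 | Contradiction |
| Pregnancy | 24 h | 10.1: 2 working days, citing 8.2 | Contradiction |
| HIV infection | 24 h | 8.1: 2 working days, citing 8.2 | Contradiction |

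Count: 3 of 5 events are contradicted outright, and 1 of 5 overlaps.

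**Size of the gap in the written limits.** Assume a Monday-to-Friday working week and no holidays. Two working days then end after these numbers of calendar days, by day of awareness: Mon 2, Tue 2, Wed 2, Thu 4, Fri 4, Sat 3, Sun 2. Subtracting the 1 day that 8.2 allows gives 1, 1, 1, 3, 3, 2, 1. The looser rule therefore permits 1 to 3 days more than the stricter one. This is the difference between two maximum allowances, not an expected delay.

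**Order of reporting.**
- 7.5.7: Monitors, TMG, Sponsor and DSMB, within 24 hours; discussion of the SAE follows at the next TMG call.
- 8.2: Monitors, Sponsor, TMG, WRAIR and DSMB, within 24 hours, then ethics committees and regulators on each authority's terms. This recipient list belongs to severe clinical events and serious or unexpected reactions; the five-event list names no recipients of its own.
- 15.2: TMG review first, then Sponsor, Steering Committee, DSMB, ethics committees and regulators; no time stated.
- 11.2: TMG calls every 2 to 4 weeks, and also on request.

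If a call is convened on request inside 24 hours, all four sections can be met and the added delay is zero. If the report waits for a scheduled call, the 24-hour limits in 7.5.7 and 8.2 are missed, and so is the 24-hour regulator limit in 7.6 where it applies. Nothing in 15.2 rules out the second course.

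**The case against.** The case on the other side has several parts, and some of them stand.

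- **Section 6.5.** A reader might count it as a fourth contradiction. The text does not require that: 6.5 is a general rule for any discontinuation, and 8.2 can be read as a tighter rule for those caused by harm. Section 6.5 mentions discussion with the TMG and reporting in one sentence but does not say that the first must precede the second.
- **Section 15.2.** A reader might infer that it keeps reports from the Sponsor or necessarily breaks the 24-hour limit. Neither is supported. The member list in 15.2 includes the Medical Experts of SMI and MUHAS (per 1.1.7, the Sponsor and its collaborating institution), and WRAIR has a representative. Sections 7.5.7 and 8.2 never say that recipients must be told simultaneously, and a call on request could be quick enough. What remains is an untimed step ahead of the DSMB, ethics committees and regulators. It could be argued that 15.2 means a later formal report, but the visible text draws no such line.
- **Text not shown.** Sections 8.2.1 and 8.2.2 are referred to but are not in the copy reviewed, and they may describe the site's route. This limits what can be said about routing. It does not help the clocks, because no added procedure makes 24 hours and 2 working days agree for the same event.
- **Consequences.** Section 7.6 suspends all immunisations pending expert review after a suspected serious adverse reaction, and pregnancy and HIV infection already stop a participant's dosing. That is real protection and limits the stakes, but it does not tell a site which deadline applies.
- **DSMB meetings.** A reader might also see a contradiction between 7.6, 9.4 and 15.5 on when the DSMB meets. It turns on what 15.5 means by a safety report, which the visible text does not define, so it forms no part of this point.

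**Conclusion.** The clock conflict holds as written for SAEs, pregnancy and HIV infection: two limits for the same event, with the looser one attributed to a section whose visible text states the stricter one. Under the working-week assumption above, the gap is 1 to 3 days. Appendix 10 gives harmonisation to 24 hours throughout as a reason for one version 2.0 change, which suggests the intended limit, but the finding rests only on current text.

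The 6.5 overlap is a matter for clarification. The 15.2 review step is a badly fixed procedure that creates a risk of delay to the DSMB, ethics committees and regulators; no breach or expected delay is claimed. The matter should be corrected because it concerns safety oversight and the remedy is cheap, but it does not threaten the trial's analysis.

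**What to change.** - **10.1:** change the SAE and pregnancy lines to 24 hours.
- **8.1:** change the HIV-infection note to 24 hours.
- **6.5:** add that a discontinuation due to a clinical or social harm event follows 8.2's 24 hours. Other discontinuations may keep 2 working days.
- **15.2:** state that TMG review must not delay the first report to the Sponsor, DSMB and regulators beyond 24 hours, and that TMG comments on grade or causality follow as an addendum.

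The cost is wording in four sections and matching site procedures; no participants, visits or samples are added. There are two downsides. First reports may go out before the TMG has reviewed grade and causality, which the addendum handles. Sites must also report pregnancy and HIV infection faster than 8.1 and 10.1 now allow, including at weekends.
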